## Abstract

**Introduction and hypotheses:**

valuation of surgical skills, both technical and nontechnical, is possible through observations and video analysis. Besides technical failures, adverse outcomes in surgery can also be related to hampered communication, moderate teamwork, lack of leadership, and loss of situational awareness. Even though some surgeons are convinced about nontechnical skills being an important part of their professionalisation, there is paucity of data about a possible relationship between nontechnical skills and surgical outcome. In robot-assisted surgery, the surgeon sits behind the console and is at a remote position from the surgical field and team, making communication more important than in open surgery and conventional laparoscopy. A lack of structured research makes it difficult to assess the value of the different analysis methods for nontechnical skills, particularly in robot-assisted surgery. Our hypothesis includes the following: (1) introduction of robot-assisted surgery leads to an initial decay in nontechnical skills behaviour during the learning curve of the team, (2) nontechnical skills behaviour is more explicitly expressed in experienced robot-assisted surgery teams than in experienced open surgery teams, and (3) introduction of robot-assisted surgery leads to the development of different forms of nontechnical skills behaviour compared with open surgery.

**Design:**

This study is a prospective, observational, multicentre, nonrandomised, case-control study including bladder cancer patients undergoing either an open radical cystectomy or a robot-assisted radical cystectomy at the Catharina Hospital Eindhoven, the Netherlands, or at the Netherlands Cancer Institute, Antoni van Leeuwenhoek Hospital Amsterdam. All patients are eligible for inclusion; there are no exclusion criteria. The Catharina Hospital Eindhoven, the Netherlands, performs on average 35 radical cystectomies a year. The Netherlands Cancer Institute, Antoni van Leeuwenhoek Hospital Amsterdam, performs on average 100 radical cystectomies a year.

**Protocol overview:**

The choice of treatment is at the discretion of the patient and the surgeon. Patient results will be obtained prospectively. Pathology results as well as complications occurring within 90 d following surgery will be registered. Surgical complications will be registered according to the Clavien-Dindo system.

**Measurements:**

Nontechnical skills will be observed using five different methods: (1) NOTSS: Nontechnical Skills for Surgeons; (2) Oxford NOTECHS II: a modified theatre team nontechnical skills scoring system; (3) OTAS: Observational Teamwork Assessment for Surgery; (4) Interpersonal and Cognitive Assessment for Robotic Surgery (ICARS): evaluation of nontechnical skills in robotic surgery; and (5) analysis of human factors. Technical skills in robot-assisted radical cystectomy will be analysed using two different methods: (1) GEARS: Global Evaluative Assessment of Robotic Skill and (2) GERT: Generic Error Rating Tool.

**Safety criteria and reporting:**

Formal ethical approval has been provided by Medical research Ethics Committees United (MEC-U), The Netherlands (reference number W19.048). We hope to present the results of this study to the scientific community at conferences and in peer-reviewed journals.

**Statistical analysis:**

Frequency statistics will be calculated for patient demographical data, and a Shapiro-Wilk test with *p* > 0.05 will be used to define normal distribution. Univariate analysis will be conducted to test for statistically significant differences in observation scores between open radical cystectomy and robot-assisted radical cystectomy cohorts across all variables, using independent sample *t* tests and Mann-Whitney *U* testing, as appropriate. A variable-selection strategy will be used to create multivariate models. Binary logistic regression will be conducted to calculate odds ratios and 95% confidence intervals for significant predictors on univariate analysis and clinically relevant covariates. Statistical significance is set at *p* < 0.05 based on a two-tailed comparison.

**Summary:**

This study uses a structured approach to the analysis of nontechnical skills using extracorporeal videos of both open radical cystectomy and robot-assisted radical cystectomy surgeries, in order to obtain detailed data on nontechnical skills during open and minimally invasive surgeries. The results of this study could possibly be used to develop team-training programmes, specifically for the introduction of the surgical robot in relation to changes in nontechnical skills. Additional analysis of technical skills using the intracorporeal footage of the surgical robot will be used to elucidate the role of surgical skills and surgical events in nontechnical skills.

## Introduction and hypotheses

Qualification and certification of the performance of surgical skills are still in a preliminary phase within all surgical specialties, including urology. There are, however, urgent calls from the government and patient organisations for well-defined proficiency standards to safeguard the quality of care [1], [2]. In addition, professionals themselves are increasingly interested to define their qualifications and improve skills [3].

Multiple research groups are investigating the relation between surgeons’ technical skills and postoperative outcome [4], [5], [6]. With the introduction of laparoscopy and the surgical robot, new and improved assessment tools of surgical skills have been developed [5], [7], [8], [9].

Although the analysis of technical surgical skills in robot-assisted surgery can lead to major improvements of postoperative outcomes [10], the possible influence of nontechnical skills on postoperative outcomes also merits attention.

The nontechnical skills needed for a successful robot-assisted radical cystectomy probably differ from those needed for an open radical cystectomy.

Even though several general assessment methods have been developed for both the entire team [11], [12], [13] and individual team members [14], [15], [16], the question remains whether these tools can accurately assess nontechnical skills in complex robot-assisted surgeries such as robot-assisted radical cystectomy. With the introduction of the Interpersonal and Cognitive Assessment for Robotic Surgery (ICARS) [17], adaptation to the robot-assisted surgical setting has started.

The introduction of the surgical robot has totally changed the traditional set-up of the operating room (OR), since the scrub nurse and the surgeon are no longer on opposite sides of the patient. In robot-assisted surgery, the surgeon is located in a separate control console during most of the surgery, and therefore direct communication with team members could be hampered. It is conceivable that loss of nonverbal communication can influence the workflow and therefore the quality of the performance, including patient's safety.

Two systematic reviews concerning the studies of nontechnical skills in minimally invasive surgery (ie, conventional laparoscopy and robot-assisted surgery) have been published [18], [19]. A wide variety of tools were used in assessments of nontechnical skills, which makes comparison of tools difficult [18], [19].

van der Vliet et al [19] advises additional research in nontechnical skills to be performed in different surgical approaches (open, laparoscopic, and robot assisted). Moreover, the use of multiple trained observers is advised for assessing audiovisual recordings of the surgical environment to identify and quantify possible interobserver reliability. The group of Gjeraa et al [18] advises systematic identification of nontechnical skills in minimally invasive surgery in order to develop effective, evidence-based team training programmes for minimally invasive surgeries.

The present study aims to perform a structured evaluation of nontechnical skills in both open and robot-assisted complex surgery, to investigate the manner in which the introduction of a surgical robot influences both nontechnical skills and surgical outcomes during the 1st year of robot-assisted radical cystectomy compared with open radical cystectomy.

In addition, analysis of technical skills in robot-assisted radical cystectomy will be performed to evaluate the possible relationship between technical and nontechnical skills. Radical cystectomy was chosen for this analysis because it is a lengthy, complex, and demanding surgery for the surgeon and other team members.

Since radical cystectomy surgeries take many hours to complete, a long-term and detailed analysis is possible per procedure. Radical cystectomy is traditionally performed using an open surgical approach (open radical cystectomy) at the Catharina Hospital Eindhoven, but recently a shift is made to robot-assisted radical cystectomy. This shift enables us to investigate in which manner nontechnical skills change during the introduction of robot-assisted radical cystectomy. The nontechnical skills during the learning curve of robot-assisted radical cystectomy in the Catharina Hospital Eindhoven will be compared with the nontechnical skills during the open radical cystectomy in the same hospital as well the nontechnical skills of an experienced robot-assisted radical cystectomy team in the Antoni van Leeuwenhoek Hospital.

These analyses will be performed in order to investigate in which manner nontechnical skills change during the introduction of the robot-assisted radical cystectomy and which factors contribute to the learning curve. Results obtained during this study could be beyond robot-assisted radical cystectomy, since the changes in operating OR set-up and the loss of nonverbal communication are universal when making the shift from open to robot-assisted surgery.

Our hypothesis includes the following:1.Introduction of robot-assisted surgery leads to an initial decay in nontechnical skills behaviour during the learning curve of the team.2.In experienced robot-assisted surgery teams, nontechnical skills behaviour is more explicitly expressed than in experienced open surgery teams.3.Introduction of robot-assisted surgery leads to the development of different forms of nontechnical skills behaviour compared with open surgery.

The results of this study could possibly be used to develop team training programmes specifically for the introduction of the surgical robot in relation to changes in nontechnical skills. Additional analysis of technical skills using the intracorporeal footage of the surgical robot will be used to elucidate the role of surgical skills and surgical events in nontechnical skills.

## Design

The present study is a prospective, observational, multicentre, nonrandomised, case-control study that will include all patients undergoing either an open radical cystectomy or a robot-assisted radical cystectomy in Catharina Hospital Eindhoven or Antoni van Leeuwenhoek Hospital.

### Time scales

The inclusion will be from January 2021 until August 2022 in both hospitals simultaneously (Fig. 1). Video collection will start once the first patient is included and will continue until the last patient has had their surgery. Follow-up data collection will start in February 2021 and will continue until December 2022. Data analysis will start in January 2022.

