### Centre details

Based on prior data, on average a total of 35 open radical cystectomies are performed yearly in the Catharina Hospital Eindhoven. Since the robot-assisted radical cystectomy has just been introduced, the total number of open radical cystectomies will be divided over the open radical cystectomy and the robot-assisted radical cystectomy modalities; it is expected that half of the radical cystectomies will be performed using a robot–assisted surgical approach. In the Antoni van Leeuwenhoek Hospital, on average a total of 50 robot-assisted radical cystectomies and 50 open radical cystectomies are performed each year. It is possible to include further hospitals in the future.

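### The stated aim is the first year of robot-assisted cystectomy, but inclusion runs 19 to 20 calendar months, is not anchored to Catharina's first robot case, and the stated comparison pools all robot cases

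*Protocol article*

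**What the plan says.** All references are to the protocol article.

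- **Aim** (Introduction and hypotheses): the influence of the robot on nontechnical skills and surgical outcomes "during the 1st year of robot-assisted radical cystectomy compared with open radical cystectomy".
- **Hypothesis 1** (same section): "Introduction of robot-assisted surgery leads to an initial decay in nontechnical skills behaviour during the learning curve of the team". The length of the learning curve is not defined.
- **Inclusion** (Time scales): "The inclusion will be from January 2021 until August 2022 in both hospitals simultaneously". For recording: "Video collection will start once the first patient is included and will continue until the last patient has had their surgery". The trigger is the first included patient at either hospital, not Catharina's first robot case.
- **Start of the robot programme:** the introduction says of Catharina's open practice, "but recently a shift is made to robot-assisted radical cystectomy"; Centre details says "Since the robot-assisted radical cystectomy has just been introduced". Neither gives a date or a count of cases already done.
- **Volume** (Centre details): "on average a total of 35 open radical cystectomies are performed yearly in the Catharina Hospital Eindhoven", and "it is expected that half of the radical cystectomies will be performed using a" robot-assisted approach.
- **Comparison:** the introduction sets Catharina's learning-curve cases against Catharina open cases and against the experienced robot team at the Antoni van Leeuwenhoek Hospital. Statistical analysis compares the open and robot cohorts by t test or Mann-Whitney test and names no term for calendar time or case order.

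**The concern.** The aim covers 12 months counted from an event, the start of robot-assisted cystectomy. The inclusion rule covers 19 to 20 months counted from a calendar date. The document does not link the two, so it does not say which Catharina robot cases answer the first-year question.

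There are two possible consequences. Cases after month 12 enter the robot cohort and are averaged with the early ones; if the decay is short-lived, this shrinks the contrast on which hypothesis 1 depends, and a null result would be hard to interpret. And if robot cases were done before January 2021, the very first ones, where an initial decay should be clearest, were never recorded, and no later analysis can recover them.

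**Working it through.** The document gives no sample size, effect size or power, so there is no stated figure to reproduce. The check is a count of expected cases, followed by an illustration of what pooling does.

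**Inputs from the document.** 35 cystectomies a year at Catharina and half robot-assisted (Centre details); window January 2021 until August 2022 (Time scales), which is 20 months if August counts and 19 if not; aim of 12 months (Introduction and hypotheses).

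**Expected Catharina robot cases**, with even accrual and the first case in January 2021:

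- Rate: 35 × 0.5 = 17.5 a year, or 1.46 a month.
- 20 months: 17.5 × 20/12 = 29.2, of which 17.5 fall in the first year and 11.7 after it; 11.7/29.2 = 40%.
- 19 months: 17.5 × 19/12 = 27.7, of which 10.2 fall after the first year; 10.2/27.7 = 37%.

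**Unknown start date** (20-month count, even accrual). If the programme began L months before January 2021, the share after its first year is 1 − max(0, 12 − L)/20. If it began k months into the window, the share is (8 − k)/(20 − k).

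| First robot case | Share after first year |
|---|---|
| 6 months into the window | 2/14 = 14% |
| 3 months into the window | 5/17 = 29% |
| January 2021 | 8/20 = 40% |
| 3 months before | 1 − 9/20 = 55% |
| 6 months before | 1 − 6/20 = 70% |
| 12 months before | 1 − 0/20 = 100% |

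**Uneven accrual**, first case in January 2021, robot share averaging one half over 20 months: 52% if the share rises linearly from 25% to 75%, and 28% if it falls from 75% to 25%.

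**Effect of pooling.** Assume a decay of d in the first year, of which a fraction r remains afterwards, with the 60/40 split above. The pooled mean difference is d × (0.6 + 0.4r). The document gives no d, so d = 0.8 SD is an assumption. Power is two-sided at 0.05, normal approximation, Φ(effect/SE − 1.96), for Catharina robot against 29.2 Catharina open cases (the other half of the volume).

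- Pooled, 29.2 against 29.2: SE = √(2/29.2) = 0.262 SD.
  - r = 0: effect 0.48, power 0.45.
  - r = 0.5: effect 0.64, power 0.69.
  - r = 1: effect 0.80, power 0.86.
- First-year robot cases only, 17.5 against 29.2: SE = √(1/17.5 + 1/29.2) = 0.302 SD, effect 0.80, power 0.75.

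The two approaches break even where (0.6 + 0.4r)/0.262 = 1/0.302, so 0.6 + 0.4r = 0.87 and r is about two thirds, whatever d is. Below that, pooling loses power; above it, pooling gains power.

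**The case against.** The strongest reply is that the inclusion window is not the learning cohort. The same window also serves the open cases at both hospitals, the experienced robot team, and hypotheses 2 and 3, none of which carries a first-year limit. Recruiting beyond month 12 is therefore no error in itself. The first-year phrase appears once, in the introduction, and is absent from the hypotheses and the design section. Which cases enter the hypothesis 1 contrast, and whether case order is modelled, could be settled in a fuller protocol or analysis plan that is not shown. All of this stands as a reason not to call the window wrong. It does not remove the mismatch between the aim and the only analysis that is stated.

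It also stands that hypothesis 1 concerns the team's learning curve and not a calendar year. At 17.5 cases a year the curve may outlast month 12, and later cases help to separate a passing decay from a lasting difference. Nor is a 12-month cut a cure: if the decay were confined to the first 10 cases (an assumption), a first-year mean would carry 10/17.5 = 57% of it, against 10/29.2 = 34% over 20 months. This favours analysis by case sequence over a calendar cut as the test of hypothesis 1.

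A reader might also infer that early robot cases were missed. The document does not show this. The planned nurse survey after five robot procedures (Study population) is compatible with few or no earlier cases, and the timeline figure was not available to this review. Early cases being missed remains a possibility that the missing start date leaves open.

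**Conclusion.** The point holds as a mismatch that should be resolved. The aim is the first year; inclusion runs 19 to 20 calendar months without an anchor to Catharina's first robot case; and the stated analysis pools the robot cases. It concerns only the Catharina robot cohort.

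The size is about 12 of 29 expected cases after the first year (40%, or 37% on a 19-month count), provided that the first case fell in January 2021 and accrual is even. Over the start dates examined the share runs from about 14% to 100%. The wording in the article suggests a start at or before the window, which under even accrual would make 40% nearer the low end.

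Two stronger readings are tempting and are not supported. One takes 40% as a fact about this cohort; the missing start date rules that out. The other says that the window dilutes the decay. Dilution needs both a decay that largely fades within the year and a pooled robot mean. If the decay persists, the later cases raise power (0.86 against 0.75 in the illustration with an assumed 0.8 SD).

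**What to change.** 1. Reconcile the aim in Introduction and hypotheses with Time scales.
2. State the date of Catharina's first robot-assisted cystectomy and the number done before January 2021.
3. Record for each Catharina robot case its sequence number and the months since the first case. Do this before the code lists are destroyed: Privacy keeps the date of surgery out of the observations, and Data collection and handling has the code lists destroyed once video results and patient characteristics are matched, so the order may not be recoverable later.
4. Answer the first-year aim with cases in the first 12 months. If cases were done before the window, restate the aim as the part of that year actually observed.
5. Test hypothesis 1 by case sequence, and keep later Catharina robot cases as a labelled later-phase group.

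The cost is some wording, two variables derived from dates that the hospital should hold, and slightly more analysis work. The first-year contrast rests on fewer robot cases (about 17 to 18 instead of 29, for a January 2021 start). No extra patients or procedures are needed, and no recorded case is discarded.

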**Fig. 1 fig0005:**

Timeline of the study.

### Study population

The surgical team in the OR will be the study population. Individual permissions will be obtained from all members of the surgical team, that is, urologists, OR nurses, and anaesthesiologists. Surgeries will be performed by three urologists, one surgeon will perform all open radical cystectomies, one surgeon will perform all robot-assisted radical cystectomies in the Catharina Hospital Eindhoven, and one surgeon will perform all robot-assisted radical cystectomies and open radical cystectomies in the Antoni van Leeuwenhoek Hospital. OR nurses for each open radical cystectomy and robot-assisted radical cystectomy in the Catharina Hospital Eindhoven will be selected based on shift schedules from the experienced dedicated team of six urology OR nurses. OR nurses for each surgery in the Antoni van Leeuwenhoek Hospital will be selected from the experienced dedicated team of six urology OR nurses. Anaesthesiologists will be selected randomly for each surgery from the total number of anaesthesiologists who have signed an informed consent form. All team members have worked together before.

After five robot-assisted radical cystectomy procedures, a survey based on the survey developed by McBride et al [20] (Supplementary material) will be held among the OR nurses in the Catharina Hospital Eindhoven in order to investigate the point of view of the OR nurses on the potential benefits of robot-assisted surgery. All surgeons will be asked what level of prior experience/training they have prior to the start of the study.

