## Statistical analysis

Frequency statistics will be calculated for patient demographical data, and a Shapiro-Wilk test with *p* > 0.05 will be used to define normal distribution. Univariate analysis will be conducted to test for statistically significant differences in observation scores between open radical cystectomy and robot-assisted radical cystectomy cohorts across all variables, using independent sample *t* tests and Mann-Whitney *U* testing, as appropriate. A variable-selection strategy will be used to create multivariate models. Binary logistic regression will be conducted to calculate odds ratios and 95% confidence intervals for significant predictors on univariate analysis and clinically relevant covariates. Statistical significance is set at *p* < 0.05 based on a two-tailed comparison. Statistical analyses will be performed using SPSS Statistics version 24 (IBM, Armonk, New York, USA).

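### At Catharina the open and robot cases belong to two different surgeons, so that comparison cannot separate the robot from the surgeon, and the planned open-versus-robot tests carry the confounding into the result.

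*Protocol article*

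**What the plan says.** Under Study population, the protocol article states "Surgeries will be performed by three urologists". It then allocates them: "one surgeon will perform all open radical cystectomies, one surgeon will perform all robot-assisted radical cystectomies in the Catharina Hospital Eindhoven". At AvL, by contrast, a single urologist covers both approaches. Each hospital draws its nurses from one dedicated pool of six. At Catharina that pool staffs both approaches.

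The Introduction and hypotheses section plans that skills during the Catharina robot learning curve "will be compared with the nontechnical skills during the open radical cystectomy in the same hospital", and also with those of the experienced robot team at AvL. Hypothesis 1 attributes an initial decay in nontechnical skills to the introduction of the robot.

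The Statistical analysis section says: "Univariate analysis will be conducted to test for statistically significant differences in observation scores" between the open and robot cohorts, "using independent sample *t* tests and Mann-Whitney *U* testing, as appropriate". It continues: "Binary logistic regression will be conducted to calculate odds ratios and 95% confidence intervals for significant predictors on univariate analysis and clinically relevant covariates". The threshold is fixed: "Statistical significance is set at *p* < 0.05 based on a two-tailed comparison". The section names no surgeon term and does not say whether the cohorts are compared within or across hospitals. Surgeon characteristics are recorded (Data collection and handling; Secondary outcome measurements), but no analytic use is stated for them.

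**The concern.** Within Catharina, knowing the approach tells you the surgeon, and the reverse. A lasting difference between the two surgeons in leadership, communication or decision style would look the same as an effect of the robot. Several primary outcomes are of the kind on which surgeons plausibly differ: NOTSS rates the surgeon, and leadership is a scored element of NOTECHS II, OTAS and ICARS (Primary outcome measurements). More operations by the same two surgeons estimate that difference more precisely but do not remove it.

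The second planned comparison, Catharina robot versus AvL robot, differs in both surgeon and hospital. The only contrast in which approach varies while the surgeon stays the same is AvL robot versus AvL open. The Introduction does not name it as a comparison, and the cohort tests as written do not isolate it. What is at stake is whether the study can attribute a difference to the robot, and so whether hypothesis 1 can be answered as worded.

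**Working it through.** The article states no sample size or power, so there is no figure of its own to reproduce.

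**Inputs from the article**
- Inclusion runs from January 2021 to August 2022, which is 20 months (Time scales).
- Catharina: 35 cystectomies a year, about half by robot (Centre details). 35 × 20/12 = 58.3 cases, or about 29 per surgeon.
- AvL: 50 robot and 50 open a year (Centre details). 50 × 20/12 = 83.3, or about 83 per approach.
- Two-sided 0.05, independent-sample tests (Statistical analysis).

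**Assumed, because the documents do not give it:** ρ, the share of score variance lying between surgeons, from 0.01 to 0.20.

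**Step 1. Can approach be separated from surgeon?** No assumed figure is needed here. For Catharina alone, a model with two surgeon indicators and one approach indicator has 3 columns but rank 2, so the approach effect cannot be estimated. With both hospitals and three surgeon indicators plus approach, the rank is 4 of 4. The variance of the approach estimate is then 0.0241 in units of residual variance, which equals 2/83. All the information comes from the AvL surgeon, and the Catharina cases add nothing.

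**Step 2. Catharina-only test, surgeons viewed as a sample, no true robot effect.** With total variance 1 and n = 29 cases per surgeon:
- true variance of the difference = 2ρ + 2(1 − ρ)/n
- variance used by the t test = 2(1 − ρ)/n
- k, the factor by which the standard error is too small = √[1 + nρ/(1 − ρ)]
- actual rejection rate = 2 × P(T > 2.003/k), with T on 56 degrees of freedom

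Worked case, ρ = 0.05: k = √(1 + 29 × 0.05/0.95) = √2.526 = 1.59, and the rate is 0.21.

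| ρ | k | rejection rate, nominal 0.05 |
|---|---|---|
| 0.01 | 1.14 | 0.08 |
| 0.02 | 1.26 | 0.12 |
| 0.05 | 1.59 | 0.21 |
| 0.10 | 2.05 | 0.33 |
| 0.20 | 2.87 | 0.49 |

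Simulation gave 0.21 for both the t and Mann-Whitney tests at ρ = 0.05, and 0.33 and 0.31 respectively at ρ = 0.10.

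**Step 3. Test pooled over both hospitals.** There are 29 + 83 = 112 cases per approach, and Catharina's weight is w = 29/112 = 0.259. The AvL surgeon appears in both cohorts and cancels.
- true variance = 2w²ρ + 2(1 − ρ)/112
- expected variance used by the test ≈ 2[(1 − ρ) + 2ρw(1 − w)]/112

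At ρ = 0.20 these are 0.0411 and 0.0157. The ratio of standard errors is 1.62 and the rejection rate about 0.23. Simulated rates were 0.06, 0.07, 0.10, 0.14 and 0.23 at ρ = 0.01, 0.02, 0.05, 0.10 and 0.20.

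**The case against.** - **The test is not restricted to Catharina.** The Statistical analysis section compares open and robot cohorts, and both hospitals are in the study. This stands. The Catharina-only rates describe a contrast that the Introduction plans but to which no test is tied, and the pooled rates are less than half as large from a share of 0.05 upward.
- **The standard error is not necessarily wrong.** If inference is confined to these particular surgeons, between-surgeon variance does not belong in the error term. This also stands. A reader might infer that the planned error is far too small whatever the view taken, but the documents do not support that: they give no between-surgeon variance, and at a share of 0.01 the inflation is small. On the fixed-surgeon view what remains is confounding, which is a problem of interpretation and is untouched by this objection.
- **Team scores are less exposed.** NOTECHS II and OTAS assess the team, the same nurse pool serves both Catharina approaches, and anaesthesiologists are assigned at random. So it goes too far to infer that any difference in surgeon style will be reported as a robot effect on every instrument.
- **A fuller analysis plan may add surgeon terms.** Clinically relevant covariates are allowed for, and an article condenses. But no covariate can undo complete aliasing at Catharina. Recorded surgeon characteristics do not help either: with one surgeon per approach they follow the approach, apart from experience gained along the way.
- **AvL is not a clean comparison.** Patient and surgeon choose the approach (Inclusion criteria), so case selection remains. It is one surgeon and one nurse pool, and about 83 per approach is a ceiling before consent and eligibility. The team is experienced, so it says nothing about introducing the robot. All of this stands and limits what the fix can deliver.

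**Conclusion.** The point holds. At Catharina, surgeon and approach are completely aliased. This follows from the stated allocation alone, and no adjustment can repair it. It matters most for NOTSS and the leadership domains, and less for team scores. The open-versus-robot tests as stated carry the confounding into their result, in full for Catharina alone and diluted when the hospitals are pooled.

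The size in error-rate terms is conditional. It requires viewing surgeons as a sample, an assumed variance share, and case numbers at expected volumes. On those terms the nominal 5% test rejects in roughly 8% to 49% of studies for Catharina alone (share 0.01 to 0.20), and roughly 10% to 23% when pooled (share 0.05 to 0.20). These rates illustrate the range; they are not properties of the plan that can be read from the documents.

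**What to change.** In the Statistical analysis section:

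1. Estimate the approach effect within surgeon, with surgeon as a fixed three-level factor. AvL robot versus open then becomes the inferential contrast for approach: same surgeon and nurse pool, up to about 83 versus 83. State that case selection remains.
2. Report Catharina robot versus open as a combined surgeon-plus-approach difference, and do not attribute its p value to the robot.
3. For hypothesis 1, add the trend over the Catharina robot surgeon's own case sequence as evidence on the learning curve. State that it shows change over successive cases and cannot show decay relative to open surgery.
4. Do not include nurse team as a random effect. There are two pools, one per hospital, and the surgeon factor already determines the hospital, so that term is not identifiable.
5. Limit conclusions to these three surgeons' teams.

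No new data are needed. The cost is in what can be claimed: the approach estimate rests on AvL cases only (up to about 166 rather than 224, from 2 × 83 and 2 × 112), the claim is narrower, and the causal wording of hypothesis 1 has weaker support.
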